### Statistical Analysis

#### Power and Sample Size

Data from our preliminary pilot study were used to estimate sample size for a comparison of intervention group means in clustered data (clustering within individual IY groups). We used a Cohen *d* effect size of 0.55, intraclass correlation of 0.04, and coefficient of variation of 0.16 in cluster (IY group) sizes. Given this is a pilot study, each primary outcome and all secondary outcomes will be tested at α=.05. Using PASS software, sample sizes of 72 in each group (total sample 144), with an estimated 9 separate IY groups with an average of 8 participants in each group and 2-sided α of .05 will achieve 82% power to detect the intervention group effect size of at least 0.55. Predicting an annual attrition rate of 20%, a full sample of 180 participants is required.

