## Abstract

**Background:**

Filipino Americans underuse mental health and preventive care services even though studies have indicated that Filipino youth experience high rates of suicidal ideation, substance abuse, and teen pregnancies, whereas adults experience immigration stress, discrimination, and depression. Evidence-based parenting interventions provided in early childhood have proven to be effective in preventing the onset and escalation of child mental health disorders. In a pilot randomized controlled trial, we found that participation in the Incredible Years Basic Parent Training Program (IY) improved parenting stress and positive parenting practices and decreased child internalizing and externalizing symptoms among Filipino families. A fully powered trial is needed to determine the efficacy of IY as a prevention program among Filipino families.

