**Methods:**

This study uses a randomized controlled 2-arm individually randomized group treatment pretest–posttest design for 180 parent–child dyads. Individuals are eligible if they are ≥18 years, live in California, and have at least one Filipino child aged 8-12 years. Consenting participants are randomly allocated to receive either the 12-week IY parenting intervention (intervention arm) or American Academy of Pediatrics’ Bright Future handouts and placed on a waitlist to receive IY posttrial (waitlist control arm). Primary outcomes include the Parent Practices Interview and the Parenting Stress Index. Secondary outcomes will be measured using the Child Behavior Checklist (completed by parent) and will include child internalizing and externalizing behaviors and total problems. Data are collected at baseline and 3- and 6-month follow-ups.

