**Conclusions:**

Our research will determine whether IY promotes positive parenting practices and prevents child internalizing and externalizing behaviors in healthy but high-risk populations such as Filipino families. It will also uplift cultural narratives and add to the evidence base for web-based parenting programs and their implementation in real-world settings. If found efficacious, IY has the potential to prevent behavioral health disparities in this understudied and high-risk Filipino population and can be scaled, adapted, and implemented in other at-risk racial and ethnic minority communities.

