### Outcomes

Our main hypothesis is that the IY will provide efficient parent training, resulting in significant improvements in parenting practices, parenting stress (primary outcomes), child problem behavior, and COVID-19–related stress (secondary outcomes).

To evaluate primary outcomes, we use the Parenting Practices Inventory [52] to assess parenting practices and physical punishment and the Parenting Stress Index–Short Form [59] to assess parenting stress. To evaluate secondary outcomes, we use the Child Behavior Checklist for Ages 6 to 18 [60]: Externalizing and Internalizing domains and Total Problems (Parent, Child). The reliability and validity of these measures have been described in the literature, with all measures previously validated in multicultural populations. Finally, owing to the COVID-19 pandemic, we also measure parental COVID-19–related stress using the Epidemic–Pandemic Impacts Inventory [61]. To assess consumer perspectives, we use parent satisfaction and participation data in IY evaluation surveys.

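### The two primary outcomes are each tested at an unadjusted .05 because the trial is called a pilot, a reason the article's own account contradicts; no success rule is stated

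*Protocol article*

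**What the plan says.** Power and Sample Size sets the testing rule and its reason in one sentence: "Given this is a pilot study, each primary outcome and all secondary outcomes will be tested at α=.05". The same paragraph gives the design inputs as a Cohen d "effect size of 0.55, intraclass correlation of 0.04, and coefficient of variation of 0.16 in cluster (IY group) sizes", with 72 participants per arm in about 9 IY groups averaging 8. It says that a "2-sided α of .05 will achieve 82% power" to detect that effect, and it takes these inputs from an earlier pilot study. Enrolment is 180 after allowing for 20% attrition.

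The pilot label also appears under Methods, Overview and under Study Design. Other places describe a different kind of study. The abstract's Background reports a completed pilot randomized trial and continues: "A fully powered trial is needed to determine the efficacy of IY as a prevention program among Filipino families". The Introduction's section on the IY program likewise presents a prevention trial as the step needed after the pilots. The abstract's Conclusions say: "Our research will determine whether IY promotes positive parenting practices and prevents child internalizing and externalizing behaviors".

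The abstract and the Outcomes section name two primary instruments: a parenting practices measure and the Parenting Stress Index. Neither section says how the two results combine into a conclusion.

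**The concern.** Calling a study a pilot can justify unadjusted testing when its results only inform a later trial. Here the pilot is in the past, this trial is powered for hypothesis tests, and the article plans to draw efficacy conclusions and speaks of scaling the program if it is found efficacious. The one reason offered for testing without adjustment therefore conflicts with the stated purpose.

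With two primary outcomes, each at .05, and no rule on what counts as success, a significant result on either could be reported as efficacy. The chance of a false claim of that kind is above the nominal 5%. The stated power also describes one outcome taken alone, not the pair.

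This is not a detail left to a fuller document. The article takes the decision and justifies it.

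**Working it through.** **Inputs from Power and Sample Size.** d = 0.55, ICC = 0.04, CV = 0.16, mean group size m = 8, n = 72 per arm, two-sided alpha .05. **From the abstract and Outcomes:** two primary instruments. **Assumed:** the correlation r between the two outcomes, which the article does not give.

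**1. The plan's own power figure**
- Design effect = 1 + ((CV² + 1)m − 1) × ICC = 1 + ((0.0256 + 1) × 8 − 1) × 0.04 = 1.288, applied to both arms.
- Noncentrality = 0.55 / √(2 × 1.288 / 72) = 2.908.
- Power, noncentral t with 142 df, alpha .05: 82.3%. The stated 82% reproduces, for a single outcome.
- 144 / 0.80 = 180, so the enrolment figure also reproduces.

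**2. Chance of at least one false-positive primary result, two tests at .05**
- Independent: 1 − 0.95² = 9.75%.
- Correlated (bivariate normal, two-sided):

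| Assumed r | At least one false positive |
|---|---|
| 0 | 9.75% |
| 0.4 | 9.3% |
| 0.5 | 9.1% |
| 0.7 | 8.3% to 8.4% |

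**3. Power with the error rate controlled, 72 per arm, both true effects 0.55**
- Alpha .025, same method (noncentrality 2.908, 142 df): 73.9%. This is Holm's first step, and so the worst case for one outcome when the other has no effect to help it.
- Holm by simulation at r = 0.4: about 80% per outcome and about 89% to succeed on at least one.
- Both must succeed, each at .05, r = 0.4: about 72% (normal approximation; 71% with 142 df).
- Keeping 82% per outcome at a fixed .025 would need about 85 per arm (normal approximation): 170 evaluable, and 170 / 0.80 = 212.5, so 213 enrolled.

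**The case against.** The strongest reply is that the inflation depends on a success rule the article does not state. The hypotheses are worded jointly, as improvement in parenting practices and in parenting stress. If both had to succeed, .05 for each would be right. If each result supported only a claim about its own outcome, each claim would carry a 5% error rate. This stands as a condition on the 8% to 10% figure. It does not remove the point, because no such rule is written and the only reason given for unadjusted testing is the pilot label.

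It is also fair to say that the abstract's Background describes the trial that is needed and does not say in terms that this is that trial. The identification is an inference, though the power calculation and the stated conclusions support it strongly.

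A reader might infer larger error rates by counting more primary tests:
- Three, because the parenting measure is used "to assess parenting practices and physical punishment".
- Eight or twelve, by also multiplying by the two follow-up times and the two delivery modes, which the Analysis Plan says will be analyzed separately.

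The article does not support these counts. It does not say that practices and punishment are separate primary scores, that both time points are primary, or that each delivery mode carries its own efficacy claim.

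Nor do the unadjusted secondary tests raise the error rate of the primary claim. The Child Behavior Checklist is parent-completed in the abstract ("Secondary outcomes will be measured using the Child Behavior Checklist (completed by parent") but covers both reporters under Outcomes ("Externalizing and Internalizing domains and Total Problems (Parent, Child"). That mismatch needs correcting as a separate point and has no effect on the primary error rate.

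**Conclusion.** The point holds for the two named primary instruments. The article fixes unadjusted testing on a rationale that its own description contradicts. If success on either primary outcome is enough to claim efficacy, the false-positive chance is 9.75% under independence and about 8% to 9% at correlations of 0.4 to 0.7. The correlations are assumptions. Any higher figure depends on scoring, time-point and delivery-mode choices that the article does not fix. The stated 82% power is arithmetically sound, but it applies to one outcome at .05.

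**What to change.** - **Label.** Remove the pilot rationale from Power and Sample Size, and reconcile the pilot label under Methods, Overview and under Study Design with the efficacy purpose in the abstract. Deleting the one clause alone would leave the contradiction in place.
- **Decision rule.** Control the two primary outcomes at a two-sided family-wise .05 with Holm. Alternatively, state that both must succeed, or test them in a fixed sequence; each of these keeps .05 per test.
- **Timing.** Results reports 103 + 60 = 163 participants with completed data collection as of December 2021, and analyses planned for completion by June 2023. Adopt the rule before outcome data are examined by arm, and record that this was so.
- **Secondary outcomes.** Report them without confirmatory claims, and bring the abstract's conclusion on child behavior into line.
- **Power.** Restate it under the chosen rule.

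**Cost.** No added participants are strictly required, but power falls. Under Holm it goes from 82% to about 80% per outcome if both effects are 0.55 (assumed r = 0.4), and to 74% in the worst case. A both-must-succeed rule has about 72% under the same assumptions. In a fixed sequence the first outcome keeps 82%, and the second can be claimed only when both are significant, so it too has about 72%.

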#### Process Evaluation

We will document participants’ and facilitators’ experiences to ensure the appropriateness and cultural relevance of the intervention. Parent satisfaction and evaluation are also measured as part of process evaluation after program participation. Qualitative methods, such as field notes are used to document and analyze the intervention’s implementation and acceptability in the target population.

## Results

Recruitment and data collection procedures are ongoing and are expected to complete by December 2022; we plan to complete data analyses by June 2023. As of December 2021, in total 103 have completed data collection in person and 60 have completed data collection on the web.

Our central hypothesis is that IY will provide efficient parent training, resulting in significant improvements in parenting practices, parenting stress, and child behavioral problems. This hypothesis is supported by a previous study in which we determined the initial estimates of effect sizes attributable to the intervention [50]. Findings of the pilot study revealed that IY had a positive impact on parenting stress, positive verbal discipline, physical punishment, and parent perceptions of their child’s externalizing symptoms, internalizing symptoms, and number of problematic behaviors [50].

Once data analysis is complete, results will be disseminated to individual partnering organizations and study participants, summarizing the results of the study. In addition, we will invite partnering organizations to a community forum aimed at sharing the results of the study and obtaining community feedback. Findings will also be submitted to a peer-reviewed journal and presented at academic conferences.

This study will provide a knowledge base for the translation of specific family-focused behavioral interventions to real-world practice settings with greater emphasis on maximizing the available resources within the contexts of local care settings (primary care settings, churches, schools, and community social service agencies) to better meet the needs of multiple stakeholders.

## Discussion

### Challenges

A few challenges arose during the study, one major obstacle being the COVID-19 pandemic. Owing to restrictions, we transitioned from in-person intervention implementation and providing the parenting group sessions in community spaces to the current remote delivery of the intervention. We worked with our community advisory board to develop the web-based protocol, and overall, families found it to be acceptable on the web. Of note, we also used materials developed by the IY developer to transition the program to the web (ie, use of web-based evaluations, tips for parenting group leaders to engage families virtually, and use of midweek individual phone calls to follow up with parents). Data collection including informed consent procedures and survey administration also transitioned from in-person to phone or Zoom conferencing communications. Unexpectedly, through the use of web-based platforms during the pandemic, we have been able to expand our outreach to different families across California and reduce time and transportation barriers to participating in the IY intervention. This web-based format seems to be more acceptable to families as it has helped overcome barriers such as transportation, commuting time to sites where in-person delivery occurred, child care, and the need for social distancing given the COVID-19 pandemic.

Another obstacle we faced was trial delay associated with use of a true community–academic partnership with numerous community partners and organizations helping to address mental health disparities in our communities. Some community partners involved have their own institutional review board and research process, which adds time to the overall regulatory review and approval. Development of statewide partnerships also requires significant time and effort, particularly when working with multidisciplinary teams including school districts, primary care clinics, and other community organizations.

### Comparison With Previous Work

Our previous work piloting IY as a community-based prevention program in partnership with gatekeepers and our community advisory board has made it possible to overcome stigma and time-related barriers [19,50]. We were also able to reach a population of at-risk children who have never been diagnosed or referred for behavioral health treatment, thus embodying the goal of prevention and early intervention. Although multiple studies have used churches and other community-based settings as means of engaging underserved, minority populations in mental health and preventative health programs [49,50,54,62-67], to our knowledge, no effectiveness trials among Filipinos have evaluated the IY as a prevention program offered in such settings. Moreover, few culturally appropriate programs specific to Filipino families exist.

To the best of our knowledge, this will also be the first study to examine the efficacy of IY as a web-based prevention program used to improve parenting practices and internalizing symptoms in school-aged children. Many of the previous studies using IY were performed with clinically referred patients and in primary care settings [68-71]. If we are able to determine that web-based IY also improves internalizing symptoms, this single intervention may be considered for use with other ethnic groups as a universal prevention strategy for healthy populations at risk for multiple behavioral problems (both externalizing and internalizing disorders).

### Future Directions

Results should suggest ways to increase the population-level effectiveness of parenting programs for minority and immigrant populations, who could benefit from such programs but tend to participate at low rates. These strategies will be used to design a future implementation trial that is attentive to the needs and preferences of parents and community stakeholders. Such strategies are critical in alleviating and eradicating behavioral health disparities seen in these populations. In addition, by transporting and evaluating effective interventions to a variety of community settings, we can provide critical information to health policy makers and public health leaders focused on making decisions about whether these interventions should be sustained.

### Conclusions

The knowledge gained from this trial will contribute to the scientific literature on preventive and early intervention programs for children at high risk for future behavioral problems as well as on the implementation of evidence-based parenting interventions in real-world settings. Very few proven interventions that target Filipino parents are available. The data will also provide important information to understand the processes underlying how IY affects parenting practices and subsequent child problem behavior among Filipino families.

This research will impact the well-being of Filipino youth and society as a whole by expanding the cultural narratives and the evidence base supporting web-based parenting interventions during middle childhood to prevent behavioral health disparities. It will allow us to identify and resolve challenges involved in implementing a behavioral parenting intervention in a large and growing immigrant population. The real value of this project is that it attempts to bridge the differences between immigrant parents and youth growing up in the United States and can serve as a model for promoting mental health equity among other immigrant communities affected by behavioral health disparities.

## Appendix

Multimedia Appendix 1 Peer Review Report from the USC Keck School of Medicine COVID-19 and Bridge Funding Program: Reviewer 1.

Multimedia Appendix 2 Peer Review Report from the USC Keck School of Medicine COVID-19 and Bridge Funding Program: Reviewer 2.

## Abbreviations

IY: Incredible Years Basic Parent Training Program
